## Abstract

**Background:**

Individuals affected by heart failure (HF) may present fatigue, dyspnea, respiratory muscle weakness, and sympathetic activity hyperstimulation of the myocardium, among other symptoms. Conducting cardiac rehabilitation (CR) programs can be associated with inspiratory muscle training. The aim of this study was to evaluate the efficacy of inspiratory muscular training (IMT) associated with a CR program on modulating myocardial sympathetic activity and maximal functional capacity, submaximal functional capacity, thickness, and mobility of the diaphragm muscle in patients with HF.

**Methods:**

We will conduct a clinical, controlled, randomized, double-blind trial that will include sedentary men and women who are 21–60 years old and who have diagnosed systolic HF and a left ventricular ejection fraction of less than 45%. Participants will be randomly assigned to one of two groups: experimental and control. The control group will follow the conventional CR protocol, and the experimental group will follow the conventional CR protocol associated with IMT 7 days a week. The two proposed exercise protocols will have a frequency of three times a week for a period of 12 weeks. The sympathetic innervation of the cardiac muscle, the maximum and submaximal functional capacity, diaphragm mobility and thickness, and the quality of life of the participants will be evaluated before and after the intervention protocol.

**Discussion:**

This clinical trial will be the first study to investigate the additional effects of IMT on CR in sympathetic hyperstimulation in the myocardium. The results of this study will contribute to developing therapeutic strategies collaborating to elucidate whether the association of IMT with CR can induce clinical benefits for patients with HF.

**Trial registration:**

ClinicalTrials.gov identifier: NCT02600000. Registered November 9, 2015. Retrospectively registered.

## Background

Heart failure (HF) is a cardiovascular syndrome with an impact on public health because of the high morbimortality rates with which it is associated. The main symptoms of HF are dyspnea, fatigue, and reduced functional capacity [1, 2]. In addition, autonomic nervous system (ANS) imbalance and aggravation of symptoms may occur as a consequence of adaptation to HF [1].

Given the importance of the ANS in patients with cardiopathy, cardiac sympathetic activity and innervation should be evaluated, and scintigraphy with metaiodobenzylguanidine labeled with iodine 123 (I^123^ MIBG) is an effective and indicated method for this type of analysis. An image obtained 15 minutes after administration of the radiopharmaceutical represents the integrity of the presynaptic nerve terminals and the density of the beta-adrenergic receptors. Four hours later, presynaptic neuronal uptake contributes to late imaging, combining information on neural function, including uptake, release, and storage of noradrenaline in the presynaptic vesicles. In addition to these, the washout rate (WR) is evaluated, constituting a parameter that shows the degree of sympathetic activity, and its increase reflects the overflow of noradrenaline into the bloodstream [3–6].

Changes in sympathetic activity also appear to be related to reduced functional capacity in these individuals as well as other factors such as the restrictive pulmonary ventilatory pattern, aggravated by the progressive increase of the cardiac area, respiratory muscle dysfunction, and peripheral musculature. However, these findings are still the subject of many investigations in order to relate respiratory dysfunctions to the reduction in exercise capacity in these individuals [6, 7].

Within this context, the inclusion of inspiratory muscular training (IMT) within cardiac rehabilitation (CR) programs has been increasingly disseminated as a good strategy to improve the clinical-functional findings in patients with HF associated with an increase in exercise performance. IMT can reduce symptoms such as dyspnea and inspiratory muscle fatigue through its effects on cardiovascular and respiratory systems yet is still not as widely used; this is perhaps because few data on its effect on the functional capacity of individuals with HF are available [8, 9].

A systematic review analyzed the effect of IMT on patients with HF, and it confirmed—among other results—improvement in maximal oxygen consumption (VO_2_) through a 12-week program. This improvement can be attributed to the delay in the development of diaphragmatic fatigue in patients with HF, leading to a reduction in the activation of additional respiratory muscles, increasing ventilatory efficiency, and reducing the blood flow required by the respiratory muscles during exercise, improving systemic vasodilation and perfusion of peripheral muscles, thereby reducing sympathetic activation [10]. However, of all the studies selected in the review, only one associated IMT with another technique (aerobic exercise) [11], and none of the studies performed a direct evaluation of myocardial sympathetic activity through radiopharmaceutical scintigraphy; it was evaluated only indirectly through spirometric parameters.

Considering the above, we hypothesized that an association of IMT with CR has modulating action on cardiac autonomic response and peripheral sympathetic activity in patients with HF and has effects on improving the maximum and submaximal functional capacity when compared with CR without IMT. It is also capable of increasing the thickness and mobility of the diaphragm muscle in these patients. Thus, the aim of this study was to evaluate the efficacy of inspiratory muscle training associated with a CR program on modulating myocardial sympathetic activity and maximal functional capacity (primary outcome), submaximal functional capacity (secondary outcome), and diaphragm muscle thickness and mobility (secondary outcome) in patients with HF.

## Methods/Design

### Objectives

The objective was to evaluate the efficacy of IMT associated with a CR program on modulating myocardial sympathetic activity and maximal functional capacity (primary outcome) as well as submaximal functional capacity (secondary outcome) and diaphragm muscle thickness and mobility (secondary outcome) in patients with HF.

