### Evaluated outcomes

The participating individuals will be evaluated on the first day of evaluation by collecting their clinical history, applying the quality-of-life questionnaire, and reading the echocardiogram. Then they will be submitted to an anthropometric evaluation (height and weight through a digital scale with anthropometer [model W300, Welmy, São Paulo, Brazil] with a capacity of 300 kg, precision of 50 g, and an anthropometer with limit of 2 m and body mass index by dividing body weight by height squared), evaluation of vital signs through a multiparameter monitor (2023, Dixtal, Manaus, Brazil), evaluation of pulmonary function through spirometry, and evaluation of respiratory muscle strength through manovacuometry. Ultrasonography will be performed on the second day to measure the diaphragm muscle thickness and mobility (secondary outcome endpoint), and maximum functional capacity (primary outcome) will be evaluated by a responsible medical professional.

The Glittre-ADL test will be performed on the third day for submaximal measurement of functional capacity (secondary outcome). Finally, the patients will be referred to a specialized hospital on the fourth day for myocardial scintigraphy (primary outcome). After all the evaluation procedures have been carried out and recorded on the corresponding file, the participants who are already randomly allocated will start their respective IMT protocols associated with CR; then the subjects will be submitted to the same evaluation process at the end of 36 sessions, along with a question that measures the degree of satisfaction with the treatment. Figure 2 and the checklist provide an overview of standardized items for clinical trials according to Standard protocol items: Recommendations for interventional trials (SPIRIT) [15].

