#### Myocardial scintigraphy with I^123^ MIBG

For myocardial scintigraphy with I^123^ MIBG, chest images will be obtained about 15 minutes after (early images) and 4 hours after (late images) receiving an intravenous injection of 185 MBq (5 mCi) of I^123^ MIBG. The images will be acquired in a tomographic gamma camera with a detector (Starcam model, General Electric Medical Systems, Milwaukee, WI, USA) with a collimator for low energy and high resolution. The energy photopeak will be centered on 159 KeV with a 20% window and 128 × 128 matrix. A static acquisition of 10 minutes will be performed in the anterior projection of the thorax in the early and late phases. A region of interest will be drawn manually over the heart (H) and over an area of nine pixels in the upper mediastinum (M) to obtain the mean counts of each of those regions, which forms the H/M ratio, it reflects the uptake of I MIBG in the nerve terminals. WR is expressed as a percentage and is calculated from the difference between early and late H/M ratios, indicating neuronal retention of the radiopharmaceutical in the area of the left ventricle. H/M values less than or equal to 1.8 and WR values greater than 19% will be considered abnormal (i.e., indicative of adrenergic hyperactivity). All patients will receive potassium iodide syrup (15 mL) orally about 1 hour before administration of I^123^ MIBG to block the thyroid gland [3]. Cardiac imaging with I^123^ MIBG is a non-invasive instrument for stratifying the risk of patients with HF by assessing sympathetic nervous system function in the heart muscle, providing treatment information and prognosis.

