### Statistical methods

Descriptive statistics will be used, and the continuous variables will be presented as means or medians, standard deviations, and 95% confidence intervals. Categorical variables will be expressed percentages and absolute numbers. The normality of the data will be evaluated through the Shapiro–Wilk or Kolmogorov–Smirnov tests. The Levene test will be used to test the variance homogeneity.

The paired *t* test will be used for normal data or the Wilcoxon test for non-normal data to compare the pre and post intervention of adrenergic tone, maximum and submaximal functional capacity, and diaphragm mobility and thickness. The unpaired *t* test or Mann–Whitney test will be used in the comparison between the groups depending on the normality of the data, and the significance level will be accepted at a *P* value of less than 0.05. The effect size will be calculated by using Cohen’s d, and the results will be interpreted on the basis of Cohen as follows: small (0.21–0.49), medium (0.50–0.79), or large (≥0.80) [23]. All participants included in the initial assessment will be considered under the intention-to-treat according to the method of last observation carried forward. The statistical analysis will be carried out with the Statistical Package for the Social Sciences, version 22.0 (SPSS Inc., Chicago, IL, USA).

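### Two outcomes are labelled primary, the MIBG variable is not named, and a flat P<0.05 applies with no rule on whether one or both must succeed

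*Protocol article*

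**What the plan says.** The Objectives section names the targets as "modulating myocardial sympathetic activity and maximal functional capacity (primary outcome) as well as submaximal functional capacity (secondary outcome"). Background repeats this. Evaluated outcomes then attaches the primary label to each construct separately: "maximum functional capacity (primary outcome) will be evaluated by a responsible medical professional", and "the patients will be referred to a specialized hospital on the fourth day for myocardial scintigraphy (primary outcome"). The second label falls on an examination, not on a variable.

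The section on myocardial scintigraphy describes an early and a late image, an H/M ratio from each, and a WR that is "calculated from the difference between early and late H/M ratios". It gives H/M and WR separate cut-offs: "H/M values less than or equal to 1.8 and WR values greater than 19% will be considered abnormal". It does not say which value is the endpoint. Ergospirometry likewise names no single exercise-test variable as primary.

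Statistical methods plans paired tests "to compare the pre and post intervention of adrenergic tone, maximum and submaximal functional capacity, and diaphragm mobility and thickness". For the randomised comparison, "The unpaired *t* test or Mann–Whitney test will be used in the comparison between the groups", and "the significance level will be accepted at a *P* value of less than 0.05". Study design sizes the trial at α 0.05 and 80% power for all study variables. The article gives no alpha split, no test order and no statement on how many primaries must succeed.

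**The concern.** A significance level controls error for a claim only once the route to that claim is fixed. Here it is open in two places: which variable stands for each primary construct, and whether success on one construct is enough. If one is enough, two chances at 0.05 give more than 5% in total. If the MIBG variable is chosen after the data are seen, there are more chances still. Background gives the early image, the late image and WR different physiological meanings, so they are not interchangeable readings of one quantity. At stake is the trial's central claim, that adding inspiratory training to rehabilitation changes myocardial sympathetic activity and maximal capacity.

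**Working it through.** **Inputs from the article.** Two primary constructs (Objectives; Evaluated outcomes). Up to three MIBG values: early H/M, late H/M and WR (scintigraphy section). Level 0.05 per comparison (Statistical methods). The article gives no correlations between these measures, so they are assumed and varied below. Tests are taken as two-sided. Only between-group comparisons are counted.

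**Starting point.** One primary test: 1 − 0.95 = 0.05, the stated level.

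**Either primary suffices, one readout each.** With independent tests the chance of at least one false positive is 1 − 0.95² = 0.0975. With correlated tests, simulated as bivariate normal statistics, it is about 9.5% at correlation 0.3, 9.0% at 0.5, 8.4% at 0.7 and 7.0% at 0.9.

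**Any MIBG value, or exercise capacity, suffices.**

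| Tests that can support the claim | Independent | With assumed correlations |
|---|---|---|
| Two MIBG values + exercise capacity | 1 − 0.95³ = 14.3% | about 10.9% to 14.3% |
| Three MIBG values + exercise capacity | 1 − 0.95⁴ = 18.5% | about 12.0% to 18.5% |

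The right-hand column takes correlations of 0 to 0.9 among the MIBG values and 0 to 0.5 between these and exercise capacity. Because the article derives WR from early and late H/M, a second version made WR their difference and kept exercise capacity independent. With the two H/M ratios correlated at 0.5 to 0.9, four tests gave 15.8% to 16.6%.

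**Both must succeed, one named variable each.** The claim fails unless both tests pass, so its error cannot exceed that of either test: at most 0.05. It is 0.05² = 0.0025 if both nulls hold and the tests are independent.

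**Check of the remedy.** Two independent tests at 0.025 give 1 − 0.975² = 0.0494, within 0.05.

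**Sample-size consequence.** The article gives no effect size, so this is illustrative: n per arm = 2(z₁₋α/₂ + z₀.₈)²/d², before losses.
- Assumed d = 0.5: 62.8, so 63 at α 0.05; 76.04, so 77 at α 0.025.
- Assumed d = 0.8: 24.5, so 25 at α 0.05; 29.7, so 30 at α 0.025.

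**The case against.** The strongest reply has three parts.

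First, this is a journal article, and multiplicity procedures are often left to an analysis plan. That covers the absence of detail. It does not cover what the article itself fixes: two primaries, one of them given as an examination, and a flat 0.05.

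Second, a reader might infer that any one significant value supports the primary claim, so that the 0.05 level simply fails. The article does not say so. Its hypothesis in Background joins the autonomic and functional effects with a conjunction, and the objective gives the pair one shared label. Requiring both is an equally available reading, and under it the error stays within 5%. This stands: the inflation is conditional, and the defect is that the rule is left open.

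Third, a reader might infer that three MIBG tests are planned, or that the error is two to three times nominal. The article supports neither. The cut-offs classify a scan as abnormal and do not list endpoints. Statistical methods names only adrenergic tone. Background comes close to selecting WR, since it presents WR as the parameter for the degree of sympathetic activity. The multiplier runs from about 1.4 (7.0/5) to 3.7 (18.5/5), depending on readouts and correlations that the article does not give. This also stands, so the larger figures show exposure if the choice stays open, not the planned analysis.

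**Conclusion.** The point holds as a conditional one. The article labels two constructs primary, leaves the MIBG variable unnamed, and accepts P below 0.05 without a decision rule. If either primary suffices with one readout each, the false-claim rate is about 7% to 9.75% for correlations from 0.9 down to 0. If any of three MIBG values may also be used, it is roughly 12% to 18.5%. If both constructs must succeed on one named variable each, there is no inflation. The correlations and the either-suffices rule are assumptions. The pre/post tests within each group are left out of these figures. If they were also read as evidence for the primary claim, they would add further chances of a false one.

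**What to change.** Before unblinding, and while the sample size is still to be calculated:

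1. Name one MIBG parameter as primary. Background supports WR as the measure of sympathetic activity. Name one exercise-test variable, for example peak VO₂.
2. State the rule for the two between-group comparisons. Either use Holm at family-wise 0.05 (smaller p below 0.025, then the other below 0.05), or require both to be significant at 0.05.
3. Make the remaining MIBG values secondary, with no confirmatory claim.
4. Carry the rule into the Study design calculation for the primaries, or state the power at the adjusted level.

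The text change is about a paragraph and alters no treatment or measurement. Each option has a price. Under Holm, no claim at all is possible unless the smaller p is below 0.025, and sizing each primary at 0.025 raises n per arm by 14 (63 to 77) at an assumed d of 0.5, or by 5 (25 to 30) at 0.8. Under the both-must-succeed rule no alpha split is needed, but joint power falls: two independent primaries with 80% power each give 0.80² = 64%, and positive correlation moves this towards 80%.

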### Study design

This is a clinical, controlled, randomized, double-blind, and feasible trial developed in partnership with the Department of Physical Therapy of the Federal University of Pernambuco (*Universidade Federal de Pernambuco*) and *Hospital das Clínicas* of Pernambuco, and the patients come from the main reference centers of Recife-Brazil for the care of patients with HF. Figure 1 represents the follow-up flowchart of the study according to the CONSORT (Consolidated Standards of Reporting Trials) [12]. The sample will be calculated from the result of the first 20 patients through the GPower 3.1 software program [13] with α of 0.05 and a power of 80%. It will be calculated for all study variables, and the largest number will be increased by 20% to compensate for possible follow-up losses.

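### The 20% uplift for losses replaces patients who leave the analysis, but baseline carry-forward keeps them in at zero change, so 80% power need not survive losses of 17–20%

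*Protocol article*

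**What the plan says.** **Sample size.** Under Study design, N is not yet fixed: "The sample will be calculated from the result of the first 20 patients through the GPower 3.1 software program". The targets are α = 0.05 and 80% power. The calculation is repeated for all study variables, and "the largest number will be increased by 20% to compensate for possible follow-up losses".

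**Missing outcomes.** Under Statistical methods: "All participants included in the initial assessment will be considered under the intention-to-treat according to the method of last observation carried forward". The same section names an unpaired t test or Mann–Whitney test between groups. It does not say whether post values or changes are compared.

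**Timing.** Under Evaluated outcomes, after the baseline work-up "the subjects will be submitted to the same evaluation process at the end of 36 sessions". The abstract agrees: the outcomes "will be evaluated before and after the intervention protocol". Inspiratory strength is rechecked weekly to set the load, but scintigraphy, ergospirometry, the Glittre-ADL test and diaphragm ultrasound have one value before and one after.

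**The concern.** A head-count allowance and baseline carry-forward treat the same patients in opposite ways. The allowance assumes that a lost patient contributes nothing and must be replaced. Carry-forward makes that patient contribute a full record with no treatment effect. Recruiting 20% more restores the number of informative patients but does not remove the zeros that pull the arms together. Where rehabilitation also moves the control arm, mixing zero and non-zero changes widens the spread as well.

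At stake is the power claimed after losses. If it is lower than 80% for an outcome, a non-significant result on that outcome would be read as stronger evidence against a benefit of inspiratory training than it is. This is separate from the bias that carry-forward puts into the estimate.

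**Working it through.** The document gives no N, effect, SD or loss rate, so there is no figure to reproduce. Only the uplift rule can be tested against the 80% target.

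**Inputs from the document:** α = 0.05, power 80%, uplift ×1.20, carry-forward of baseline, unpaired comparison.

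**Assumptions:** two-sided test, 1:1 allocation, equal loss L in both arms unrelated to outcome, similar SD at both times, standardised effects d = 0.5, 0.8 and 1.0, and a control-arm gain of 0 or 0.5 SD.

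**1. Base n per arm for 80% power (t test), then ×1.20 rounded up.** d = 0.5: 64 → 77. d = 0.8: 26 → 32. d = 1.0: 17 → 21.

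**2. Reference: lost patients leave the analysis.** The uplift holds while 1.2(1 − L) ≥ 1, that is L ≤ 1/6 = 16.7%. Power = Φ[2.802 × √(1.2(1 − L)) − 1.960], where 2.802 = 1.960 + 0.842.
- L = 1/6: Φ(0.842) = 80.0%
- L = 20%: Φ(0.785) = 78.4%

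**3. Post values, baseline carried forward, no control gain.** The difference becomes (1 − L)δ and the SD is taken as unchanged. Power = Φ[2.802 × (1 − L) × √1.2 − 1.960].
- L = 1/6: Φ(2.557 − 1.960) = 72.5%
- L = 20%: Φ(2.455 − 1.960) = 69.0%
- Break-even: (1 − L)√1.2 = 1, so L = 1 − 1/√1.2 = 8.7%
- Multiplier needed at 20% loss: 1/0.8² = 1.5625, against the stated 1.20

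**4. Change scores.** Lost patients add zeros, which dilute the mean but can also reduce the variance. Per arm the variance is (1 − L)(1 + L·m²), with m the arm's mean change in SD units. For d = 0.8 and L = 1/6:
- no control gain: average m² = (0 + 0.64)/2 = 0.32; variance 0.833 × 1.053 = 0.878; power Φ(2.557/√0.878 − 1.960) = 77.9%
- 0.5 SD control gain: average m² = (0.25 + 1.69)/2 = 0.97; variance 0.833 × 1.162 = 0.968; power Φ(2.557/√0.968 − 1.960) = 73.9%

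At L = 20% the same formula gives 75.8% and 71.0%.

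**5. Simulation check.** 20,000 trials per cell at the uplifted n of step 1, pre–post correlation 0.7. Each patient was lost at random with probability L and set to baseline, and an unpaired t test was run. Ranges are over the three values of d.

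| Loss | Post, no control gain | Post, 0.5 SD gain | Change, no control gain | Change, 0.5 SD gain |
|---|---|---|---|---|
| 1/6 | 72–73% | 69% | 80–81% | 74–77% |
| 20% | 67–69% | 63–65% | 77–79% | 72–74% |

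Simulated change-score power runs a little above the formula, in part because n is rounded up.

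**6. Variables that do not set N.** Take a primary outcome with d = 0.8, compared on post values at 20% loss with no control gain, so its diluted effect is 0.8 × 0.8 = 0.64 (noncentral t).
- Another variable with d = 0.7 sets N: 34 → 41 per arm, and the primary keeps 82%.
- Another variable with d = 0.65 sets N: 39 → 47 per arm, and the primary keeps 87%.

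**7. If the first-20 estimate is already diluted.** Sizing on 0.64 gives 40 → 48 per arm and about 87% power.

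**The case against.** The strongest reply is that nothing has been miscalculated. Multiplying by 1.2 is a conventional allowance, no loss rate is stated, and the full protocol may give one. The reply has further support:

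- The uplift is enough for small losses, up to about 9% on post values without control gain.
- If changes are compared and controls barely move, power is about what it would be had lost patients simply left. The shortfall from carry-forward is then close to nil.
- N is the largest over all variables, so only the variable that sets it is held to 80%. Others start higher.
- If the first 20 patients are analysed with carry-forward, the sizing effect already contains the dilution.
- The control gain of 0.5 SD is assumed; the document gives no figure.

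All of these stand, and they limit the size of the point. They do not remove the mismatch, because both rules are stated and no passage connects them. A control arm with no change is also the most favourable case: both arms receive 36 supervised rehabilitation sessions, so some gain is plausible.

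It could also be said that the real fault is carry-forward itself, and that correcting it would dispose of this point. That is true, and it is why the preferred fix starts there.

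**Conclusion.** The point holds conditionally. For the variable that sets N, and provided the first-20 estimate is not already diluted, 80% power is generally not maintained at the 17–20% losses that a 20% uplift implies. The size depends on the comparison:

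- **Post values:** about 72% at 1/6 loss and 69% at 20%, lower if the control arm improves.
- **Change scores:** about 80% and 78% with no control gain, essentially the same as if lost patients left; about 76% and 73% with a 0.5 SD control gain.

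These figures rest on a two-sided test, 1:1 allocation and equal, non-informative loss.

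A reader might infer that the uplift never compensates for losses, or that the trial is underpowered for myocardial sympathetic activity and maximal functional capacity. The document supports neither. It gives no loss rate, and nothing shows that a primary outcome sets N. A variable with a clearly larger standardised effect than the one setting N may keep 80% or more.

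**What to change.** **Preferred.** In Statistical methods, make the primary between-group analysis a baseline-adjusted comparison of observed post values, with multiple imputation or carry-forward as a sensitivity analysis. In Study design, state that the 20% uplift maintains the planned power for losses up to 16.7%.

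**Otherwise.** If carry-forward stays primary, drop the claim that the uplift compensates for losses. Say whether post values or changes are compared, and whether the first-20 estimates include carried-forward values. Restate power after losses from (1 − loss) × δ at the loss rate observed so far.

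**Cost.** A few sentences, a short recalculation and no additional patients. The first route changes the primary analysis, so it should be fixed before group results are seen; it adds a little analysis work and relies on an explicit missing-data assumption. The second leaves any shortfall in place and gives a less favourable stated power, but an accurate one.
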